## Methods/Design

### Study design

The design is a multi-centre interrupted time series study. The interrupted time series (ITS) model follows the Cochrane Effective Practice and Organisation of Care Review Group criteria for short time series [45]. This type of series consists of pre- and post-intervention phases and needs to have at least three observation points in the pre-intervention phase and three in the post-intervention phase. Every data point needs to have at least 30 observations. The six data points needed will be strategically spread over pre- and post-measurement periods. The study will be conducted during a period of three years. An advantage of an ITS design is that it allows for the statistical investigation of potential biases such as secular trends in the estimate of the effect of the intervention [46]. ITS is also more feasible than a Randomized Controlled Trial in measuring the effect of interventions that require organisational change to a health care delivery system, which is the case in the WINGS study [45].

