3) To further assure a successful implementation process, a finally designed Ward-Oriented Pharmacy service will be presented to all personnel in the participating departments. A one-month introduction period will be used to fine-tune the interventions. To keep the participating departments informed about the progress of the study, periodic evaluations will be planned and a newsletter will be distributed. After 7 months we expect the implementation of a Ward-Oriented Pharmacy service to be finalised.

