### Sample size calculation and data analysis

The power-calculation for this study was based on the expected incidence of 15 ADEs per 100 hospitalisations and a clinically relevant 50% reduction by a Ward-Oriented Pharmacy service in the post-measurement period. This assumption was made based on the findings of two controlled studies that assessed active clinical pharmacists participation in medical teams on the wards, showing a reduction of 66% and 78% respectively [12,13]. To be able to identify a significant reduction from 15 ADEs to 7.5 ADEs per 100 hospitalisations, 496 patient admissions are needed, equally divided between pre- and post-measurement period (α = 0,05 and β = 0,8). This sample size enables to identify a reduction of 19 ADEs or more from the expected 38 ADEs in 248 admissions during the pre-measurement period.

Descriptive statistics will be used to summarise patient characteristics for the three participating hospitals and to check for any imbalance in variables between pre- and post-measurement groups. By comparing the pre- and post-measurement periods, the effect of a Ward-Oriented Pharmacy service will be analysed using a suitable generalised linear model for a short interrupted time series. Adjustment will be made for any case mix imbalances between pre- and post-measurement periods and background trend in the ADE rate over time.

Exploratory analyses are also planned to examine the effect of factors like age, sex, length of hospital stay, Charlson Co-morbidity Index Score [58], renal function on the primary and secondary outcomes. For this purpose unadjusted univariate and adjusted multivariate Poisson regression analyses are planned.

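### The 80% power claimed for 496 admissions belongs to a one-sided before/after comparison without a time term, not to the trend-adjusted analysis planned

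*Protocol article*

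**What the plan says.** The section on sample size and data analysis contains both halves of the problem.

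- **Size.** It starts from an "expected incidence of 15 ADEs per 100 hospitalisations" and a halving of that rate, and concludes: "496 patient admissions are needed, equally divided between pre- and post-measurement period". The error rates are given as "α = 0,05 and β = 0,8", where the second figure can only mean power of 80%. Sidedness is not stated.
- **Analysis.** The next paragraph assigns the effect estimate to a generalised linear model of the short interrupted time series (ITS) type, adjusted for case mix and for "background trend in the ADE rate over time".

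The Study design section sets the layout at a minimum of three points on each side and at least 30 observations per point, within a three-year study: "The six data points needed will be strategically spread over pre- and post-measurement periods". It gives investigation of secular trends as an advantage of the design. The Intervention section adds: "After 7 months we expect the implementation of a Ward-Oriented Pharmacy service to be finalised". The article gives neither the calendar of the six points nor the length of the gap between the two phases.

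**The concern.** The power statement and the effect analysis concern two different estimates. The first is a plain difference between two periods. The second is a step at the interruption after a time trend has been removed. With three points on each side, all early points are before and all late points are after, so phase and time carry much of the same information. Estimating both widens the interval for the step.

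The study has no concurrent control group, so the trend term is its main protection against secular change. The effect on preventable ADEs is one of its primary goals. If the power for the trend-adjusted effect is well below the stated figure, a true halving of ADEs could easily come out non-significant, and a reader relying on the stated 80% would take that as evidence against the service.

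**Working it through.** **Inputs from the article.** Rates 0.15 and 0.075; 248 admissions per period; alpha 0.05; power 80%; three points before and three after; three years.

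**Assumptions, not in the article.** Equal numbers per point (248/3 ≈ 82.7 admissions, so 12.4 expected ADEs per point before and 6.2 after); Poisson counts; one linear trend whose true slope is zero; no overdispersion or hospital clustering.

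**Step 1: reproduce the 496.** For a difference of two Poisson rates, n per period = (z_α + z_power)² × (0.15 + 0.075)/0.075² = (z_α + z_power)² × 40.

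- One-sided: (1.645 + 0.842)² × 40 = 247.3, so 248 per period and 496 in total. This is an exact match.
- Two-sided: (1.960 + 0.842)² × 40 = 314.0, so 628 in total.
- Two-proportion formulas give 438 (one-sided), 490 (one-sided, continuity correction), 556 (two-sided) and 608 (two-sided, continuity correction).

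At 248 per period the standardised difference is 0.075/√(0.225/248) = 2.490. Power is Φ(2.490 − 1.645) = 80% one-sided and Φ(2.490 − 1.960) = 70% two-sided. No version contains a time term.

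**Step 2: the same contrast on the log-rate scale, no trend.** Expected ADEs are 37.2 before and 18.6 after. V₀ = 1/37.2 + 1/18.6 = 0.0806, so SE(log rate ratio) = 0.284. Power is Φ(0.693/0.284 − z_α) = 68% two-sided and 79% one-sided. This is the like-for-like baseline for the next step.

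**Step 3: add a linear trend.** In a log-link Poisson model with intercept, time and phase, the variance of the phase effect is V = V₀ + d²/S. Here d is the distance between the mean times of the two phases. S is the sum of squared deviations of time within phases, each point weighted by its expected ADEs. Because d²/S cannot be negative, the trend term never improves precision.

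For six equally spaced points, d = 3 and S = 12.4 × 2 + 6.2 × 2 = 37.2. So V = 0.0806 + 9/37.2 = 0.3226, SE = 0.568, and the inflation is 0.3226/0.0806 = 4.0.

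| Timing of the points (months, except first row) | d | S | SE | Variance inflation | Power two-sided | Power one-sided |
|---|---|---|---|---|---|---|
| Equally spaced (any unit) | 3 | 37.2 | 0.57 | 4.0 | 23% | 34% |
| 0, 1, 2 / 9, 10, 11 | 9 | 37.2 | 1.50 | 28 | 7% | 12% |
| 0, 3, 6 / 13, 16, 19 | 13 | 334.8 | 0.77 | 7.3 | 15% | 23% |
| 0, 6, 12 / 19, 25, 31 | 19 | 1339.2 | 0.59 | 4.3 | 21% | 32% |
| 0, 13, 14 / 21, 22, 35 | 17 | 2269.2 | 0.46 | 2.6 | 33% | 45% |
| 0, 14, 14.5 / 21.5, 22, 36 | 17 | 2520.3 | 0.44 | 2.4 | 35% | 47% |
| 0, 16, 17 / 18, 19, 35 (no gap) | 13 | 3385.2 | 0.36 | 1.6 | 48% | 61% |

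Rows two to six have a 7-month gap between the last point before and the first point after.

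**Step 4: checks.** Simulation with 3,000 replicates gave 23.8% two-sided for the equally spaced layout. In the layouts where a slope-change term was also tried, the SE was the same or larger. With equal spacing, an observed ratio of 0.50 would have a 95% interval of 0.50 × exp(±1.96 × 0.568), about 0.16 to 1.5.

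**The case against.** The strongest reply is that the article leaves the model open. It speaks only of a suitable model and of comparing the two periods. The form of the trend, the time unit and the calendar of points are details that a full protocol or analysis plan would normally hold. That is right as far as it goes: their absence is not a fault here, and no single power figure can be computed from the article. It does not remove the mismatch. The article itself prints both the number and the commitment to adjust for trend, and no choice of calendar makes that adjustment free.

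Several stronger readings do not hold:

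- *The true power is 7–23%.* The lower end needs points one month apart around a 7-month gap, which the article nowhere states. The 7 months is when implementation is expected to be complete, not a stated gap between measurements. The upper end belongs to equal spacing.
- *The variance rises at least fourfold.* Four is the value for equal spacing, not a minimum. Points grouped near the interruption give 2.4 to 2.6 with a 7-month gap and 1.6 in one layout without a gap.
- *The whole drop from 80% is due to the trend.* The 80% is one-sided. Two-sided power is already about 70% with no trend term, so one-sided figures must be compared with one-sided.
- *The points should therefore be equally spaced.* Among the layouts tried, equal spacing does worse than points placed near the interruption.

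Nothing in the article shows that a null result would be misreported or the trend term dropped after the data are seen. Those are risks, not stated intentions.

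**Conclusion.** The power statement is wrong as written. The 80% for 496 admissions applies to an unadjusted, one-sided before/after contrast, while the planned effect analysis removes a background trend. Under the assumptions listed, none of the timings tried brings the trend-adjusted effect to 80%, one-sided or two-sided. How far it falls short cannot be fixed from the article, because the timing of the points decides it, as the table shows. Overdispersion or clustering by hospital would lower the power further. The finding does not show that the ITS design is unsuitable or that the trend adjustment should be given up.

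**What to change.** In the section on sample size and data analysis:

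1. State whether alpha is one-sided or two-sided.
2. Say that 80% power at 496 admissions holds only for the unadjusted one-sided contrast between the two periods (about 70% two-sided).
3. Give the power, or the expected confidence-interval width, for the trend-adjusted effect under the measurement calendar actually used, with the assumed trend form and numbers per point.
4. State that a non-significant trend-adjusted result is inconclusive and will be reported with its confidence interval.

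The cost is a short rewrite and one calculation. No extra patients are needed to make the statement correct. The downside is a much less favourable stated power.

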## Discussion

Clinical Pharmacy as practised in Anglo-Saxon countries has shown to be successful in reducing preventable ADEs in various hospital patient populations [12-15]. In this study, the effect of a Ward-Oriented Pharmacy service on preventable ADEs in elderly inpatients will be investigated. The Ward-Oriented Pharmacy service is an on-ward pharmacy service based on the successful Clinical Pharmacy practice but tailored to the Dutch hospital setting. The Ward-Oriented Pharmacy service will include multifaceted interventions implemented in Internal Medicine wards by hospital pharmacists. Adapting Clinical Pharmacy practice to the Dutch hospital setting is necessary, because Clinical Pharmacy entails a full-time participation of clinical pharmacists in medical teams on the wards, a time investment that is not feasible within the current organisation of Hospital Pharmacy in the Netherlands. This applies also to many other European countries [19]. Moreover, active on-ward participation of pharmacists in medical teams is a practice Dutch physicians are not familiar with. This could raise barriers that also need to be considered.

The results of the WINGS study will add insight into the effectiveness of Ward-Oriented Pharmacy on the reduction of ADEs in elderly inpatients. Also the extent to which this service is feasible in the Dutch setting will be explored. By measuring ADEs across the process of admission and subsequent hospitalisation, the extent to which ADEs are recognised and appropriately managed by treating physicians will be investigated. Especially in elderly patients, ADE awareness is essential to be able to practice the safest possible pharmacotherapy [37].

The method of data collection and chart review used in the WINGS study differs from the standard trigger-tool based chart review method used in other ADE studies [35]. According to the standard method, only charts with one or more triggers are subjected to further review by a physician. Therefore, only a selection of ADEs can be scored and this selection depends on the predefined selection of triggers used in the first step of data collection and examination procedure. In contrast, the trigger-tool based CRF in this study serves only as an aid to help the experts. Trigger-tools have shown to be able to increase the detection of ADEs and can be computerised or used manually [60]. We will use manual screening for ADE triggers in patient files instead of electronic trigger-tools, because by the manual method, the narrative information, such as progress notes or discharge letters, can be screened. Symptoms like constipation, dizziness, falls and hypotension are examples of ADE triggers in narrative information sources. By subjecting all included patients to further review and applying the above described method, a more sensitive ADE assessment by the experts is expected. In our setting, where the magnitude of medication risks in elderly inpatients is unclear, such a comprehensive approach is needed to gain detailed insight into this problem. The time-consuming character of our method is not a barrier, because it is used for research purposes.

In the WINGS study, the primary outcome (ADE) is assessed by using a combination of implicit expert judgment with structured causality assessment based on the WHO-UMC system [56]. Because the WHO-UMC system was developed for ADRs causality assessment, we added or discarded items to design a causality assessment strategy for ADEs and therefore assessment of ADRs and preventable ADEs. Furthermore, both errors of omission and commission are considered as causes of preventable ADEs in our assessment [50].

The expert judgment is the most popular and most widely used method, even given limitations like lack of reproducibility, poor inter- and intra-rater agreement and a lack of standardised clinical evaluation. Algorithms for ADR causality assessment have been developed to overcome the limitations of expert judgment [61]. However, as mentioned before, ADE assessment in elderly patients could be complicated by factors like multi-morbidity, polypharmacy and atypical presentation of diseases. Therefore, opinion of clinically experienced reviewers, who are able to weigh drug causation considering all these factors, is essential. In order to do so, less flexible and less specific algorithms are not suitable in this study. It has also been shown that reproducibility of results from the use of such algorithms can drastically decrease, yielding low inter-rater variability, because clinical judgment is always necessary to be able to answer all the questions included [61].

To improve the validity of the method used in this study, we have taken three measures:

1) by using a CRF we help the experts to standardise their clinical evaluation, 2) by combining implicit review followed by structured causality assessment we lower the subjectivity of the expert's decisions 3) by deployment of the same expert team in ADE assessment in the pre- and post-measurement phases the problem of low inter-rater agreement seen in studies using expert judgment can be partly overcome [55].
